### Procedure for unblinding if needed {17b}

Not applicable as this is an open-label study.

## Data collection and management

### Plans for assessment and collection of outcomes {18a}

All study-related procedures among pregnant women and their newborns will be performed in District Hospitals including pre-enrolment screening and post-delivery evaluation of the mother and child. Study visits will be conducted at the same time as planned ANC visits when possible. Outcomes may be abstracted from medical records and women will be tracked over the study using a unique study ID combined with their District Hospital-assigned medical record ID and biometric data collection. All participating District Hospital units will have the appropriate training and diagnostic capability to capture trial endpoints. Data will be entered into RedCap Cloud collection forms.

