### Strategies to improve adherence to interventions {11c}

To reduce the chances of a participant being lost to follow-up, prior to randomization attempts should be made to obtain contact information from each participant. The following actions must be taken if a participant fails to return to the study site for a required study visit:The study-site personnel must attempt to contact the participant to reschedule the missed visit as soon as possible, to counsel the participant on the importance of maintaining the assigned visit schedule, to ascertain whether the participant wishes to or should continue in the studyBefore a participant is deemed lost to follow-up, the investigator or designee must make every reasonable effort to regain contact with the participant (where possible, 3 telephone calls, e-mails, and/or SMS/text, or local equivalent methods). These contact attempts should be documented in the participant’s medical recordsShould the participant continue to be unreachable, they will be considered to have withdrawn from the study

Women will receive 12,000 Rwanda Francs for each study visit, equal to roughly $12 USD.

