**Primary**	
• Assess **adverse maternal/fetal outcomes in pregnant women** randomized to receive the 2-dose Ebola vaccine regimen (Ad26.ZEBOV, MVA-BN-Filo (group A)) and in control women (unvaccinated pregnant women (group B))	• Frequency of maternal death, spontaneous abortion, stillbirth, pathways to preterm birth (premature preterm rupture of membranes, preterm labor, insufficient cervix, provider initiated preterm birth), pre-eclampsia/eclampsia, antenatal bleeding and post-partum hemorrhage from randomization until 6 weeks post-completion/termination of pregnancy
• Assess **adverse neonatal/infant outcomes in neonates/infants** born to women randomized to receive the 2-dose Ebola vaccine regimen (Ad26.ZEBOV, MVA-BN-Filo (group A)) and in neonates/infants born to control women (unvaccinated pregnant women (group B))	• Frequency of major congenital malformations, small for gestational age (SGA), low birth weight, preterm birth, neonatal death, and failure to thrive in infants measured from birth until 14 weeks of age

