#### Sample size {14}

The primary outcomes of this unpowered study are adverse maternal, fetal, and neonatal/infant outcomes in vaccinated pregnant women and their neonates. The sample size was determined based on feasibility and estimated background incidence of the primary study outcomes. Background rates for adverse maternal and fetal outcomes in pregnancy are not comprehensively available for Rwanda for all events of interest. However, the Rwanda Demographic Health Survey (2014–2015) [16] provides rates of maternal death (210 per 100,000 live births) and neonatal death (20 per 1000 live births). With the proposed sample size of 1000, the probability of observing at least 1 AE occurring at a rate of 1/1000 is 63%. If no (S)AE (this includes adverse maternal/fetal outcomes) is observed in the vaccine group (*N* = 1000), this would provide 95% confidence that the true incidence is no more than 0.3%.

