### Plans to promote participant retention and complete follow-up {18b}

Study participants are pregnant women and they have regular clinic visits; therefore, there are no foreseen major issues with participant retention at this stage. The following study tools/materials/initiatives are available to further ensure participant retention:

Participants will be reimbursed for travel costs to and from the study site.Study visits and contacts will allow sites to develop and maintain a relationship with participantsParticipants are being mobilized from communities within the catchment area of the study site to make participant out-reach feasibleMobile messaging technology (MOTECH) will be utilized to stay in close contact with participants. This is automated phone messaging system that will use follow-up messages to participants and reminders of when to return to clinics for a visitCommunity engagement staff of study site will reach out proactively and directly to study participants for any missing visits

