## Statistical methods

### Statistical methods for primary and secondary outcomes {20a}

For purposes of analysis, the following populations are defined:Full analysis set (FAS): The FAS will include all randomized participants. All safety analyses will be made on the FASPer-protocol immunogenicity (PPI): The PPI population will include all randomized and vaccinated participants for whom immunogenicity data are available excluding participants with major protocol deviations expecting to impact the immunogenicity outcomes

Of note, women enrolled from Umurinzi will be analyzed separately. No formal statistical testing is planned. The number and percentage of participants screened, enrolled, randomized, receiving two vaccine doses, and completing follow-up will be summarized by study arm.

Baseline demographic characteristics (including gestational age and obstetric risk assessment) will be tabulated overall and by study arm.

The frequency and percentage of women for whom at least one of the indicated adverse outcomes was reported as a primary endpoint (see above) will be summarized by study group. For each separate adverse maternal/fetal and adverse neonatal/infant outcome, the number and percentage of participants who experience at least 1 occurrence of the given event will also be tabulated by study group (groups A and B, and their infants). The verbatim terms used in the CRF by investigators to identify AEs will be coded using the Medical Dictionary for Regulatory Activities (MedDRA). The reporting of the categorical safety data will include the incidence, severity, relatedness, and type of AEs. Continuous safety parameters will be analyzed descriptively (showing the mean, standard deviation, median, and quartiles [Q1 and Q3]).

For participants from group A, all reported AEs, events-related diary information (solicited local at injection site and systemic, and unsolicited) with onset within 4 weeks post dose 1 or dose 2 vaccination (i.e., treatment-emergent AEs) will be included in the analysis. For each AE, the number and percentage of participants who experience at least 1 occurrence of the given event will be summarized. Of note, solicited and unsolicited AEs will not be collected for group B participants.

Summaries, listings, datasets, or participant narratives may be provided, as appropriate, for those participants who die, who discontinue intervention due to an AE, or who experience a severe or a serious AE.

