### Methods in analysis to handle protocol non-adherence and any statistical methods to handle missing data {20c}

The safety analysis will be done on the full analysis dataset. No data will be imputed.

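### Unreachable women are recorded as withdrawn, and looking up their outcomes in hospital records is optional, so primary events among them can be missed

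*Protocol article*

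**What the plan says.** All references are to the protocol article.

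- **Strategies to improve adherence to interventions {11c}.** Before a participant is classed as lost to follow-up, staff make every reasonable effort to regain contact, described as "where possible, 3 telephone calls, e-mails, and/or SMS/text, or local equivalent methods". The closing sentence then says that a woman who is still unreachable is regarded as withdrawn from the study.
- **Plans for assessment and collection of outcomes {18a}.** "Outcomes may be abstracted from medical records and women will be tracked over the study using a unique study ID", which is "combined with their District Hospital-assigned medical record ID and biometric data collection". Abstraction is permitted. It is neither required nor ruled out for unreachable women.
- **Plans to promote participant retention {18b}.** Community staff contact women directly about missed visits, and "there are no foreseen major issues with participant retention at this stage". No loss rate is given.
- **Table 1.** The maternal and fetal primary outcomes, including maternal death, spontaneous abortion and stillbirth, run "from randomization until 6 weeks post-completion/termination of pregnancy". The infant outcomes, including neonatal death, run to 14 weeks of age.
- **Statistical methods {20a} and {20c}.** "The FAS will include all randomized participants", all safety analyses use that set, and "No data will be imputed".

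**The concern.** Being unreachable is not a refusal. The article elsewhere treats the two as different things: the consent section {26a} describes withdrawal as a voluntary act of the participant, and the adverse event section {22} lists refusal and loss to follow-up as separate reasons why no more information can be obtained. The closing sentence of {11c} gives both the same label.

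The label matters because several primary outcomes can themselves make a woman unreachable. For maternal death the link is direct. For a pregnancy or infant loss it is a plausible inference, not something the article states. The contact steps named in {11c} are messages to the woman herself; no check of hospital records or vital status is named there. A record link exists, but nothing requires that it be used for her. Since nothing is imputed, an event that nobody looks up does not enter the primary counts. The trial is meant to support a label change on the strength of descriptive rates, so complete ascertainment of rare severe outcomes carries much of its value.

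**Working it through.** **1. The plan's own figures.** Sample size {14} gives a 63% probability of at least one event at a rate of 1/1000 with N = 1000, and an upper bound of 0.3% if no event is seen.

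- 1 − 0.999^1000 = 0.632, which reproduces 63%.
- 1 − 0.05^(1/1000) = 0.00299, which reproduces 0.3% (a one-sided 95% bound).

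Both assume that the outcome of all 1000 women is known.

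**2. Effect on precision.** With an assumed 5% unascertained (n = 950):

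- 1 − 0.999^950 = 61.3%
- 1 − 0.05^(1/950) = 0.315%

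With 10% unascertained (n = 900) the figures are 59.4% and 0.332%. The loss of precision is small. The issue is bias.

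**3. Share of events missed.** Let *d* be the fraction of women whose outcome is never ascertained and *k* the risk in those women relative to the rest. Then:

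share missed = *kd* / [(1 − *d*) + *kd*]

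The article gives neither *d* nor *k*, so both are assumptions.

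| *d* | *k* | Calculation | Share missed |
|---|---|---|---|
| 2% | 1 | 0.02 / 1.00 | 2.0% |
| 5% | 1 | 0.05 / 1.00 | 5.0% |
| 5% | 3 | 0.15 / 1.10 | 13.6% |
| 5% | 5 | 0.25 / 1.20 | 20.8% |
| 10% | 3 | 0.30 / 1.20 | 25.0% |

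**4. In events per arm.** Section {14} gives "maternal death (210 per 100,000 live births") and neonatal death at 20 per 1000 live births. Taking about one live birth per woman, 1000 women give 1000 × 0.0021 = 2.1 expected maternal deaths and 1000 × 0.02 = 20 expected neonatal deaths.

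At *d* = 5% and *k* = 3, the expected numbers missed are 0.136 × 2.1 = 0.29 maternal and 0.136 × 20 = 2.7 neonatal deaths. The neonatal death rate would read (20 − 2.73)/1000 = 1.73% over all randomized women, or (20 − 2.73)/950 = 1.82% among those followed, against a true 2.0%. At *d* = 2% and *k* = 1, 0.04 maternal and 0.4 neonatal deaths would be missed.

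**5. The texts side by side.** {11c} assigns a final status without a record check. {18a} supplies the link needed for one but leaves its use open. {18b} adds outreach, which reduces how many women reach that status but does not change the status given. No section joins the three into a required procedure.

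**The case against.** Much of the case on the other side stands.

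- No section says that record abstraction or data collection ends once a woman is deemed withdrawn. Section {22} requires unresolved serious adverse events to be followed after participation ends, and {26a} mentions a participant register for long-term follow-up. A reader might infer that the rule in {11c} shuts off the record route and that these outcomes *are* lost. The article supports only that they *can* be.
- Tracing is more than three calls. {11c} asks for every reasonable effort, and the community staff in {18b} may well learn of a death or a miscarriage. Women also plan to deliver at a study hospital whose units are trained to capture the endpoints.
- Hospital records will not show every early loss, home death or infant event elsewhere, so the remedy is incomplete.
- A reader might also infer a spurious difference between arms. Loss could differ in an open-label trial: from day 1 to day 85, group A outside the immunology subset has six visits and group B four. But the payment per visit is the same for all women, and no loss rate is given for either arm. Even an assumed 3% against 7% loss, with a true composite risk of 20% in both arms and no event recorded for any lost woman, gives 0.20 × 0.97 = 19.4% against 0.20 × 0.93 = 18.6%. That gap of 0.8 points compares with a 95% half-width of 1.96 × √(2 × 0.2 × 0.8 / 1000) = 3.5 points. An arm difference is possible but not shown.
- The full protocol may contain a fuller tracing procedure, and leaving descriptive safety counts unimputed is a normal choice.

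None of this removes the stated rule. The article itself says that unreachable women are deemed withdrawn, and it makes the available look-up optional.

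**Conclusion.** The point holds as an inexpensive improvement to a stated rule, and its anchor is the closing sentence of {11c}. That sentence merges two different statuses, and the optional wording in {18a} does not guarantee that the outcomes of the women affected are sought. Primary events among them can therefore be missed, or counted as no event where the denominator is all randomized women.

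The size cannot be fixed from the article. The illustrations run from 2% of events missed (2% loss, equal risk) to 14% (5% loss, threefold risk) and 25% (10% loss, threefold risk). These loss fractions mean outcomes that are never ascertained by any route, so outreach and voluntary abstraction would lower them. That lost women carry a higher risk is a reasonable inference, not a documented fact.

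**What to change.** 1. In {11c}, replace the closing sentence: a participant who cannot be reached is recorded as lost to follow-up, and only an explicit refusal is recorded as withdrawal of consent.
2. In {18a}, turn the option into a requirement. For every randomized woman who has not withdrawn consent, pregnancy outcome, maternal vital status and infant status are sought from District Hospital and antenatal clinic records through the existing record number, and through the community outreach in {18b}, to the end of each primary endpoint period.
3. Report women lost to follow-up, women who withdrew consent, and women or infants with unascertained outcomes separately by arm.

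The cost is two sentences of protocol wording and chart review by existing staff for the women concerned. Outcomes taken from charts are less detailed than those assessed at a visit, so their source should be flagged. Some events outside the two hospitals will still be missed, which is why the unascertained number should be shown.

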### Plans to promote participant retention and complete follow-up {18b}

Study participants are pregnant women and they have regular clinic visits; therefore, there are no foreseen major issues with participant retention at this stage. The following study tools/materials/initiatives are available to further ensure participant retention:

Participants will be reimbursed for travel costs to and from the study site.Study visits and contacts will allow sites to develop and maintain a relationship with participantsParticipants are being mobilized from communities within the catchment area of the study site to make participant out-reach feasibleMobile messaging technology (MOTECH) will be utilized to stay in close contact with participants. This is automated phone messaging system that will use follow-up messages to participants and reminders of when to return to clinics for a visitCommunity engagement staff of study site will reach out proactively and directly to study participants for any missing visits

### Data management {19}

Steps to be taken to ensure the accuracy and reliability of data include the selection of qualified investigators and appropriate study sites, review of protocol procedures with the investigator and study-site personnel before the study, and periodic monitoring visits by the sponsor. Written instructions will be provided for collection, handling, storage, and shipment of samples. Guidelines for CRF completion will be provided and reviewed with study-site personnel before the start of the study.

The sponsor will review CRF for accuracy and completeness during on-site monitoring visits and after transmission to the sponsor; any discrepancies will be resolved with the investigator or designee, as appropriate. After the upload of the data into the study database, they will be verified for accuracy and consistency with the data sources. The Data Management Plan (DMP) details data entry and coding procedures, secure storage, data range checks for data values, manual data review procedures, source data verification, and system and user query generation and resolution guidelines.

### Confidentiality {27}

The collection and processing of personal data from participants enrolled in this study will be limited to those data that are necessary to fulfill the objectives of the study. These data will be collected and processed with adequate precautions to ensure confidentiality and compliance with applicable data privacy protection laws and regulations. Appropriate technical and organizational measures to protect the personal data against unauthorized disclosures or access, accidental or unlawful destruction, or accidental loss or alteration must be put in place. Sponsor personnel whose responsibilities require access to personal data agree to keep the identity of participants confidential.

The informed consent obtained from the participant includes explicit consent for the processing of personal data and for the investigator/institution to allow direct access to his or her original medical records (source data/documents) for study-related monitoring, audit, IEC/IRB review, and regulatory inspection. This consent also addresses the transfer of the data to other entities and to other countries.

### Plans for collection, laboratory evaluation, and storage of biological specimens for genetic or molecular analysis in this trial/future use {33}

Samples collected in this study may be stored for up to 15 years (or according to local regulations) for additional research. Samples will only be used to understand Ad26.ZEBOV and MVA-BN-Filo, to understand EVD, to understand differential intervention responders, and to develop tests/assays related to Ad26.ZEBOV and MVA-BN-Filo and EVD. The research may begin at any time during the study or the post-study storage period. Stored samples will be coded throughout the sample storage and analysis process and will not be labeled with personal identifiers. The informed consent obtained from the participant includes information on the time period that samples will be stored. Participants may withdraw their consent for their samples to be stored for research.

## Statistical methods

### Statistical methods for primary and secondary outcomes {20a}

For purposes of analysis, the following populations are defined:Full analysis set (FAS): The FAS will include all randomized participants. All safety analyses will be made on the FASPer-protocol immunogenicity (PPI): The PPI population will include all randomized and vaccinated participants for whom immunogenicity data are available excluding participants with major protocol deviations expecting to impact the immunogenicity outcomes

Of note, women enrolled from Umurinzi will be analyzed separately. No formal statistical testing is planned. The number and percentage of participants screened, enrolled, randomized, receiving two vaccine doses, and completing follow-up will be summarized by study arm.

Baseline demographic characteristics (including gestational age and obstetric risk assessment) will be tabulated overall and by study arm.

The frequency and percentage of women for whom at least one of the indicated adverse outcomes was reported as a primary endpoint (see above) will be summarized by study group. For each separate adverse maternal/fetal and adverse neonatal/infant outcome, the number and percentage of participants who experience at least 1 occurrence of the given event will also be tabulated by study group (groups A and B, and their infants). The verbatim terms used in the CRF by investigators to identify AEs will be coded using the Medical Dictionary for Regulatory Activities (MedDRA). The reporting of the categorical safety data will include the incidence, severity, relatedness, and type of AEs. Continuous safety parameters will be analyzed descriptively (showing the mean, standard deviation, median, and quartiles [Q1 and Q3]).

For participants from group A, all reported AEs, events-related diary information (solicited local at injection site and systemic, and unsolicited) with onset within 4 weeks post dose 1 or dose 2 vaccination (i.e., treatment-emergent AEs) will be included in the analysis. For each AE, the number and percentage of participants who experience at least 1 occurrence of the given event will be summarized. Of note, solicited and unsolicited AEs will not be collected for group B participants.

Summaries, listings, datasets, or participant narratives may be provided, as appropriate, for those participants who die, who discontinue intervention due to an AE, or who experience a severe or a serious AE.

For participants from group A, solicited local (at injection site) and systemic AEs will be summarized descriptively. The overall frequencies per as well as frequencies according to severity and duration will be calculated for solicited AEs. In addition, the number and percentages of participants with at least one solicited local (at injection site) or systemic AE will be presented. Frequencies of unsolicited AEs, separately for all and vaccination-related only, will be presented by System Organ Class and preferred term, while those of solicited AEs will be presented only by preferred term.

Laboratory data will be listed by type of laboratory test. Reference ranges and markedly abnormal results will be used in the listing of laboratory data. Laboratory analyses will not be conducted routinely after screening.

Vital signs including temperature, pulse/heart rate, and blood pressure (systolic and diastolic) will be summarized over time, using descriptive statistics and/or graphically. The percentage of participants with values beyond clinically important limits will be summarized.

Physical examination findings will be listed.

The immunogenicity analyses will be performed on the PPI set. Descriptive statistics of the anti-EBOV GP binding antibody (including responder rate, geometric means with their corresponding 95% CIs, median, interquartile range, minimum, maximum, as applicable) will be calculated for continuous immunologic parameters at each time point. Graphical representations of immunologic parameters will be prepared, as applicable. Frequency tabulations will be calculated for discrete (qualitative) immunologic parameters at each time point.

Detailed statistical methodology for all analyses are described in the statistical analysis plan (SAP).

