## Interventions

### Explanation for the choice of comparators {6b}

The comparator group is unvaccinated pregnant women (group B). Robust data on background rates of adverse pregnancy outcomes are not available. Therefore, the unvaccinated pregnant women in group B (a non-interventional control) are important to establish the frequency and magnitude of changes in clinical endpoints that may occur in the absence of active vaccination during pregnancy (group A). Group B comparator women will receive the study vaccine after pregnancy termination.

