### Participant timeline {13}

See Tables 2, 3, 4, and 5 for the participant schedule of activities and visit timeline.

**Table 2 Tab2:** Schedule of activities—women in group A

Visit #	1	2	3	4	5	6	7 ^a^	8	9	10	11^a^	EE
**Visit timing**^**p**^		**Dose 1**	**Dose 1** ** + 7 days**	**Dose 1 + ** **28 days**	**Dose 2**	**Dose 2 + ** **7 days**	**Dose 2 + ** **21 days**	**Dose 2 + ** **28 days**	**Pregnancy completion/** **termination**	**PP 1 + 42**	**Dose 1 + ** **365 days**	**Early** **Exit**
**Visit day and window**	** − 28 to 1**	**D1**	**D8 ± 3 days**	**D29 ± 7 days**	**D57** ** − 14 days, + 28 days**	**D64 ± 3 days**	**D78 ± 3 days**	**D85 ± 7 days**	**PP 1** ^b^ ** + 2 days**	**PP 43** ^c^ ** ± 14 days**	**Dose 1 + 365 ± 28 days**	
**Visit type**	Screening	**DOSE 1 group A**	Safety	Safety	**DOSE 2 group A**	Safety	Immuno	Safety	Safety and immuno	Safety	Safety and immuno	Early exit
Assessment of understanding	•											
Written informed consent (ICF) ^d^	•											
Inclusion/exclusion criteria	•	•										
Demographics ^**e**^	•											
Medical and obstetric history ^f^; pre-pregnancy and pre-study meds	•											
Physical examination ^f^	•				•					•		•
Obstetric exam ^f^	•	•			•				•			•^o^
Targeted physical exam ^f^		•	•	•		•	•	•			•	
Vital signs ^f^ incl. body temperature	•		•	•		•	•	•	•	•	•	•
Urine pregnancy test ^g^	•											
Hematology, chemistry ^g^	•											
Urine dipstick/urinalysis ^g^	•	•		•	•			•				
Syphilis, HIV, hepatitis B and C, malaria screening^g^	•											
Obstetric ultrasound ^h^	•	•^h^						•				•^o^
Biometric scan	•	•	•	•	•	•	•	•	•	•	•	•
Contact information	•	•	•	•	•	•	•	•	•	•	•	•
Randomization		•										
Pre-vaccination symptoms ^i^												
Vaccination		•			•							
30 min post-vaccination observation ^j^		•			•							
Solicited AE collection ^k^		•	•		•	•						
Unsolicited AE collection ^k^		•	•	•	•	•	•	•				
Distribution of participant diary, rulers and thermometers ^k^		•			•							
Participant diary review by site staff			•			•						
Adverse maternal, fetal outcomes		•	•	•	•	•	•	•	•	•		
SAE recording		•	•	•	•	•	•	•	•	•	•	•
Concomitant medications ^l^	•	•	•	•	•	•	•	•	•	•	•	•
Delivery history ^m^									•			
Post pregnancy physical examination ^m^									•			
Laboratory assessments^n^									•			
Acceptability questionnaire									•	•		•
Group A immunology subset supplemental procedures (*N* = 150)	**1**	**2**	**3**	**4**	**5**	**6**	**7**	**8**	**9**	**10**	**11**	

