Humoral immunogenicity sample (serum)							•		•			
Cord blood sample									•		•	
Breast milk sample (*N* = 50)										•		

pre-dose;

pre- and post-dose

^a^Visits 7 and 11 for group A immunology subset participants only

^b^PP 1 refers to the day of pregnancy completion/termination. Visit 9 (PP 1) should occur on the day of pregnancy completion/termination or within 2 days

^c^Visit 10 (PP 43) scheduled to occur at routine 6 week post-partum visit. For women from group A not part of the immunogenicity subset, this visit will be the end of the trial

^d^Must be signed before first study-related activity

^e^Maternal demographic information to be collected at screening includes date of birth, race/ethnicity, education level, geographical location/residence, occupation, household size (number of persons living in the same home), and international travel history

^f^Information to be collected for medical and obstetric history, physical exams, and vital signs is specified in the protocol

^g^Urine dipstick for protein and glucose will be performed at these visits. If results 1 + or greater, then additional work-up for pre-eclampsia or gestational diabetes may be warranted

^h^Ultrasound not required at visit 2 if screening (visit 1) ultrasound completed within past 10 days and no other indication for ultrasound

^i^Investigator must check for acute illness or body temperature ≥ 38.0 °C at the time of vaccination. In such cases, the participant may be vaccinated at later time point

^j^Participants will be closely observed for a minimum of 30 min post-vaccination

^k^In all women of group A, solicited AEs (reactogenicity) and unsolicited AEs will be assessed 7 days post each dose and 28 post each dose respectively

^l^Includes any medical treatment/medications given to the mother during delivery (e.g., antibiotic prophylaxis)-specifying names of medications administered

^m^Information to be collected for delivery history and post-pregnancy examination is specified in the protocol

^n^Any routine laboratory assessment performed at time of delivery and other laboratory tests as medically indicated

^o^Not required if participant is not pregnant

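### Primary maternal/fetal outcomes are assessed at 5 (subset 6) in-pregnancy visits after day 1 in group A and 3 in group B, so short-lived events may be found less often in controls

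*Protocol article*

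**What the plan says.** Table 1 gives the maternal/fetal endpoint the same window in both arms, "from randomization until 6 weeks post-completion/termination of pregnancy". The statistical methods section {20a} reports each outcome as a crude proportion of women: "the number and percentage of participants who experience at least 1 occurrence of the given event will also be tabulated by study group". It reports women with any of the listed outcomes in the same way.

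In the schedules of activities (Participant timeline {13}), the row "Adverse maternal, fetal outcomes" is ticked at visits 2 to 10 for group A (Table 2) and visits 2 to 7 for group B (Table 3). One of the group A visits is restricted by a footnote: "Visits 7 and 11 for group A immunology subset participants only".

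The section on comparators {6b} calls group B "important to establish the frequency and magnitude of changes in clinical endpoints that may occur in the absence of active vaccination during pregnancy". Section {20a} also states that solicited and unsolicited adverse events are not gathered in group B, and section {20b} plans no further analyses. On sources other than the study visit, section {18a} says "Outcomes may be abstracted from medical records" and "Study visits will be conducted at the same time as planned ANC visits when possible".

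**The concern.** The proportion of women with at least one recorded event depends on how often someone asks, unless every event is remembered until the next contact or reaches a record that is searched in both arms. Group A is asked more often. At D57, as the tables are printed, it also has a full physical and an obstetric examination where group B has a targeted physical examination. Unsolicited event collection gives a brief bleed or a bout of preterm labor in group A a further route into the database. The trial is open-label.

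Group B is there to supply a background rate that the article says is not robustly available elsewhere. If that rate is low for short-lived outcomes because controls were asked less often, a modest excess in group A could appear with no vaccine effect, in a study meant to support relaxing the label for pregnancy.

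**Working it through.** **The plan's own figures.** The article gives no figure on ascertainment. Its two precision figures reproduce: 1 − 0.999^1000 = 63.2% (stated 63%) and 1 − 0.05^(1/1000) = 0.299% (stated 0.3%). This point depends on neither.

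**Visit count (Tables 2 and 3, nominal days, after day 1 and before delivery).**

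- Group A: D8, D29, D57, D64, D85 = 5. The subset of 150 adds D78 = 6.
- Group B: D29, D57, D85 = 3.
- Both arms then share pregnancy completion and the 6-week post-partum visit.

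These are maxima. If pregnancy ends on day 40, 60, 70, 80 or 100, the counts are 2, 3, 4, 4 and 5 in group A (subset 2, 3, 4, 5 and 6) against 1, 2, 2, 2 and 3 in group B. Group A is higher each time.

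**Illustrative model (an assumption, not in the article).** Onset is uniform over the 84 days from D1 to D85, there is no vaccine effect, and an event is recorded only if a scheduled visit falls within w days after onset. The no-effect ratio is then days covered in A divided by days covered in B. For w = 7, group A covers 5 × 7 = 35 days, the subset 6 × 7 = 42 and group B 3 × 7 = 21, giving 35/21 = 1.67 and 42/21 = 2.00. For larger w, overlapping days count once.

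| w (days) | A | A subset | B | A/B | subset/B |
|---|---|---|---|---|---|
| 7 | 35 | 42 | 21 | 1.67 | 2.00 |
| 14 | 56 | 63 | 42 | 1.33 | 1.50 |
| 21 | 77 | 77 | 63 | 1.22 | 1.22 |
| 28 | 84 | 84 | 84 | 1.00 | 1.00 |

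The longest gap between group B visits up to D85 is 28 days, so recall to the previous visit removes the difference.

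**Allowing for records.** Let a share s of events depend on study visits and let the rest reach records in both arms. With w = 7, coverage is 35/84 = 0.417 in A and 21/84 = 0.25 in B, and the ratio is (1 − s + 0.417s)/(1 − s + 0.25s). This gives 1.05 for s = 0.25, 1.13 for s = 0.5 and 1.67 for s = 1.

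**Restricting to shared visits.** Remove group A events first identified at D8, D64 or D78.

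- w = 7: D29, D57 and D85 leave 21 days in A (also 21 in the subset) against 21 in B, ratio 1.00.
- w = 28: D8 and D64 each take 7 days out of A, so 84 − 14 = 70 and 70/84 = 0.83. In the subset D78 takes a further 14, so 56/84 = 0.67.

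Under no effect, the all-visit table therefore errs at or above 1 and the shared-visit table at or below 1.

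**The case against.** The strongest reply is that nothing in the article says a visit captures only recent events. The endpoint is cumulative with one window for both arms, the arms share five contacts after day 1, and antenatal visits and medical records are open to both. On the model above, recall back to the previous visit leaves no bias at all. That stands, and it is why the effect can only be called possible. It does not dispose of the point, because record abstraction is permitted and not required, and the article states no look-back rule.

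It is also fair that few outcomes are exposed. Maternal death, spontaneous abortion, stillbirth, provider-initiated preterm birth and post-partum hemorrhage do not depend on the number of in-pregnancy visits. Urine dipstick and ultrasound days match between arms, standard case definitions apply, and labor and delivery staff do not know the arm. That last safeguard does not reach events recorded at in-pregnancy study visits.

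A reader might extend the point to vital signs, since the plan says "The percentage of participants with values beyond clinically important limits will be summarized". The text does not support that. The preceding sentence has vital signs summarized over time, so a per-visit percentage is at least as natural a reading, and the printed table does not settle how many readings group A has. No ratio should be put on it.

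It may be said that extra tables belong in the SAP. The detail does, but the unequal schedule and the summary measure are both fixed here.

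**Conclusion.** The imbalance in scheduled assessments is a fact: 5 (subset 6) against 3, with unsolicited event collection in group A only and no allowance in the by-arm percentages. Its effect is a risk confined mainly to antenatal bleeding and preterm labor that stops. With no vaccine effect, the ratio for events arising between D1 and D85 lies between 1.0 and about 1.67 (2.0 in the subset). The upper end requires both a 7-day capture window and no source other than the study visit. If half of events reach records anyway, it is 1.13. After D85 the two schedules coincide, so a ratio over the whole endpoint window would be nearer 1.

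Two stronger readings are tempting. One is that controls are under-counted as a matter of fact; the documents do not show this, because they neither limit recall nor rule out complete abstraction. The other is that a group A excess could never be told from a true effect, or that the plan risks false reassurance. Any bias raises the vaccinated arm's rate relative to controls, so on its own it cannot hide harm. Severity, relatedness, serious adverse events in both arms and independent committee review also bear on interpretation. What remains is an avoidable ambiguity in reading a modest excess of short-lived outcomes.

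**What to change.** Keep the planned all-visit table as the main table. For the exposed maternal/fetal outcomes, add one by-arm table limited to events identified at visits both arms have (D29, D57, D85, pregnancy completion, 6 weeks post-partum) or from medical records. Show group A events first identified only at D8, D64 or D78 in a separate row.

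State beside it that the shared-visit table alone can understate group A: with full recall and no effect the ratio falls to 0.83, or 0.67 in the subset. It also moves out of the comparison events first found at the visits one week after each dose, where a true effect would matter. It must not replace the main table; the two are read together as bounds.

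If a cumulative percentage of women with any vital-sign reading beyond limits is compared by arm, use only visits with the same timing in both.

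The cost is one extra table per exposed outcome, with no new visits or procedures. It requires that the case report form show the visit or source at which each event was first identified. The article does not say whether it does, so this should be confirmed.
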